## Abstract

**Background:**

Endovascular abdominal aortic repair (EVAR) and thoracic endovascular aortic repair (TEVAR) have become the first-line treatment for aortic diseases, but current evidence is uncertain regarding whether a percutaneous approach has better outcomes than cutdown access, especially for patient-centered outcomes (PCOs). This study is designed to compare these outcomes of percutaneous access vs. cutdown access after endovascular aortic repair.

**Method:**

The SWEET study is a randomized, controlled, single-blind, single-center non-inferiority trial with two parallel groups in two cohorts respectively. After eligibility screening, subjects who meet the inclusion criteria will be divided into Cohort EVAR or Cohort TEVAR according to clinic interviews. And then participants in two cohorts will be randomly allocated to either intervention groups receiving percutaneous access endovascular repair or controlled groups receiving cutdown access endovascular repair separately. Primary clinician-reported outcome (ClinRO) is access-related complication, and primary patient-centered outcome (PCO) is time back to normal life. Follow-up will be conducted at 2 weeks, 1 month, 3 months postoperatively.

**Discussion:**

The choice of either percutaneous or cutdown access may not greatly affect the success of EVAR or TEVAR procedures, but can influence the quality of life and patient-centered experience. Given the very low evidence for ClinROs and few data for PCOs, comparison of the percutaneous vs. cutdown access EVAR and TEVAR is essential for both patient-centered care and clinical decision making in endovascular aortic repair.

**Trial registration:**

Chinese Clinical Trial Registry ChiCTR2100053161 (registered on 13th November, 2021).

## Introduction

Aortic diseases consist of degenerative, inflammatory, traumatic, infectious and congenital disorders, among which aortic aneurysm and aortic dissection are two common and life-threatening diseases. In terms of abdominal aortic aneurysm alone, the worldwide prevalence in people aged 75 to 79 was 2,275 per 100,000 in 2010 (1). Alarmingly, 34% patients died before reaching a hospital or during first admission once aneurysm ruptured (2). As for aortic dissection, the pre-hospital and in-hospital mortality was even higher, and reached 39% (2). Therefore, timely and correct intervention is quite essential. According to the European Society for Vascular Surgery (ESVS) 2019 guidelines for abdominal aortic aneurysm and 2017 guidelines for thoracic aortic diseases, endovascular abdominal aortic repair (EVAR) or thoracic endovascular aortic repair (TEVAR) is the first-line treatment option for aortic diseases when the anatomy is appropriate, and this recommendation is Class I with level of evidence A (3, 4).

Endovascular intervention techniques continue to evolve, and it is now feasible to obtain percutaneous femoral artery access and close the arterial puncture site with a vascular closure device remotely. Compared with conventional cutdown access, percutaneous procedure was reported to have potential advantages, involving lower risks of access site infection and lymphorrhagia, as well as shorter operation time (5). However, endovascular aortic repairs usually require large-profile sheath in the femoral arteries, which can carry challenges to percutaneous access closure, especially in patients with calcified or small femoral arteries (6, 7). Failure in percutaneous closure can lead to surgical repair. The risk-benefit balance in the choice of access procedures is still uncertain.

Most previous data were mainly based on cohort studies of different periods with low level of evidence (8). Only four randomized controlled trials (RCTs) were published comparing two types of access during EVAR, but all trials were judged to have low or very low certainty of evidence with high risk of bias (9–12). In addition, no RCTs have been published comparing two types of access in TEVAR. Though the recent meta-analysis revealed comparable access complication rates between two access procedures, it is noteworthy that no studies reported patient-centered outcomes (PCOs), for instance, patient's experience and quality of life after surgery (13). Considering its relatively small impact on prognosis and large impact on quality of life, PCOs may be a new perspective to shed light on the selection of access procedures in EVAR or TEVAR.

Given the current gap in evidence, this study intends to design a single-center, parallel, non-inferiority, randomized controlled trial in a 1:1 ratio, comparing both clinician-reported outcomes (ClinROs) and PCOs between percutaneouS vs. cutdoWn accEss in patients after Endovascular aorTic repair (SWEET) in two cohorts (EVAR and TEVAR).

## Materials and methods

### Study setting

The SWEET trial is a single-center study conducted at West China Hospital, Sichuan University in Chengdu, China. The protocol is reported in accordance with the Standard Protocol Items: Recommendations for Interventional Trials (SPIRIT) guidelines (14). The SPIRIT checklist is shown in Supplementary Table S1 (Supplementary Material). The trial was registered in the Chinese Clinical Trial Registry (registration number: ChiCTR2100053161) on 13th November, 2021.

### Participants

#### Recruitment

The participant characteristics derived from the PICO framework are presented in Supplementary Table S2 (Supplementary Material). Eligible patients with an indication for endovascular aortic repair will be informed concisely about the study by the attending resident. Subsequently, a trained research nurse will provide the consent and inform the patient in detail prior to the procedure. After careful consideration by the patient and relatives, the informed consent form will be signed prior to randomization in case of participation. Withdrawal from the study is permitted at any time for any reason, and it will not cause any consequence. To encourage participation, we will provide priority or fast track for outpatient appointments, follow-up assessment and consultation. If extra transportation costs are incurred due to the study, they will be paid by the sponsor.

#### Eligibility criteria

The study population consists of two independent cohorts: Cohort EVAR and TEVAR. The inclusion criteria of participants in Cohort EVAR are as follows: a. patient scheduled for EVAR because of abdominal aorto-iliac artery aneurysm or dissection, b. patient has signed informed consent. The inclusion criteria of participants in Cohort TEVAR are similar: a. patient scheduled for TEVAR because of thoracic aortic aneurysm or type B aortic dissection, b. patient has written informed consent.

The following exclusion criteria are applicable to both Cohort EVAR and TEVAR: a. emergent cases with ruptured or impending rupture aortic diseases, b. subjects with heavily calcified common femoral artery (more than 70% circumferential calcification).

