**Figure 1 F1:**
[figure not shown]
Flow of participants randomly assigned to percutaneous groups and cutdown groups.

Block randomization stratified by age and body mass index (BMI) using permuted blocks of random sizes will be performed with 1:1 allocation in both cohorts. Randomization sequence is generated by SPSS 26.0 statistical software by a biostatistician. The block size will be concealed until the primary endpoints are analyzed. An independent research coordinator will be responsible for keeping the sequentially numbered allocation sequence list, and will inform the surgeons about the assigned access procedure prior to intervention. To avoid performance bias, every surgeon must have had 10 or more ProGlide procedures, and experience of at least 20 surgical cutdowns to expose the access artery is also needed.

Obviously, trial participants and operating team cannot be blinded to the allocation. The data will be entered into the computer in separate tables by employees outside the research team so that the analysts can analyze data without knowing the allocation information. Therefore, only data analysts are blinded in this study.

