### Data collection and management

#### Data collection methods

Baseline data required are shown in Supplementary Table S5 (Supplementary Material). Age, sex, BMI, comorbidity etc., should be collected before assignment to achieve maximum balance between groups. Anatomical characteristics of aortic aneurysm, aortic dissection and access artery that have potential impact on treatment success and prognosis should also be routinely measured by the operating team with computed tomography angiography (CTA). In particular, the heavily calcified femoral artery, defined as an estimated over 50% area of calcification in the superficial surface, needs more attention of investigator (7). So does the severe tortuous iliac artery, which is defined as any portion of iliac artery with tortuous angle more than 90° so that visually doubled or more on a single slice of axial CTA (18).

All patients after surgery will be examined for access-related complications during the everyday ward rounds and dressing changes. After discharge, the remaining primary and secondary outcomes can be gotten by telephone interviews and outpatient re-examination over several months. Quality of life scores will be quantified by EQ-5D questionnaire during follow-up, which reduces the variability in life quality assessment by various researchers. The EQ-5D questionnaire evaluates overall quality of life from 5 dimensions of mobility, self-care, usual activities, pain/discomfort, anxiety/depression, with each dimension ranging level 1 to 5. And its reliability and validity have been verified in many studies (19, 20).

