#### Analysis of primary and secondary outcomes

Generalized linear model (GLM) will be used to compare continuous primary and secondary endpoints, and further adjustment for age, gender, BMI and femoral artery calcification will be performed by multivariate GLM analysis. Logistic regression using generalized estimating equations (GEE) will be applied to compare categorical primary and secondary endpoints. Using multivariate GEE models, the subsequent analysis will be adjusted for age, gender, BMI and femoral artery calcification. The access-related complications are counted and analyzed by the number of femoral accesses instead of the number of patients.

To address heterogeneity among study population, pre-specified subgroup analyses will be performed in the following populations: heavily calcified femoral artery vs. lightly calcified femoral artery, tortuous iliac artery vs. non-tortuous iliac artery, obesity or overweight vs. normal weight, smoking vs. none, elderly or octogenarian vs. younger population.

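### Disease type (aneurysm or dissection) is left out of the adjusted recovery-time model, which gives up some precision and leaves a chance imbalance uncorrected

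*Protocol article*

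**What the plan says.** Under Eligibility criteria, Cohort EVAR takes a "patient scheduled for EVAR because of abdominal aorto-iliac artery aneurysm or dissection" and Cohort TEVAR a "patient scheduled for TEVAR because of thoracic aortic aneurysm or type B aortic dissection". Emergencies with rupture or impending rupture are excluded from both.

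Under Assignment of intervention, the allocation method is "Block randomization stratified by age and body mass index (BMI) using permuted blocks of random sizes". Indication is not a stratum.

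Under Analysis of primary and secondary outcomes, continuous endpoints are compared by GLM, and "further adjustment for age, gender, BMI and femoral artery calcification will be performed by multivariate GLM analysis". Categorical endpoints are modelled by GEE with the same four covariates. Indication is not among the listed subgroups either.

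Under Data collection methods, the operating team is to measure "Anatomical characteristics of aortic aneurysm, aortic dissection and access artery that have potential impact on treatment success and prognosis". None of the aortic disease characteristics enters a planned model.

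**The concern.** The protocol fixes its covariates by name, so this is not a detail left open for an analysis plan. BMI and femoral calcification suit the access-complication endpoint: the Discussion names obesity and calcified femoral arteries as suspected causes of percutaneous failure. The same set is then used for the number of days until the patient resumes normal life or work, an outcome that can plausibly depend on the aortic disease as well as on the groin wound. The same applies to length of stay and EQ-5D scores.

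Two things are at stake. Variation due to disease type stays in the residual and widens the interval. And if the arms happen to differ in their share of dissections, no planned analysis takes the resulting shift out. The sample size was derived from access complications because no patient-centered data existed, so the primary patient-centered outcome has no power calculation of its own and little reason to give up precision.

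**Working it through.** **Inputs from the protocol (Sample size).** The groups are 60 per arm in Cohort EVAR and 50 in Cohort TEVAR. To reproduce them, use the unpooled non-inferiority formula n = [pC(1-pC) + pT(1-pT)] × (1.645 + 0.842)² / (m - (pT - pC))².
- EVAR: 0.1747 × 6.183 / 0.1417² = 53.8, so 54; 54/0.9 = 60.
- TEVAR: 0.1572 × 6.183 / 0.148² = 44.4, so 45; 45/0.9 = 50.

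These figures come out at one-sided alpha 0.05. How the text words alpha is a separate matter and does not affect what follows.

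**Assumptions, because the documents give no values.**
- Share with dissection, p: 30-50%, with 10% as a low case for Cohort EVAR.
- Difference in mean recovery time between the diseases, δ: 0.25, 0.5 or 1.0 within-disease SD, taken as what remains after the four planned covariates.
- Equal within-disease SDs, a model linear in days, and 1:1 allocation not stratified by disease.

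**Step 1: chance imbalance.** The SD of the between-arm difference in dissection share is √(2p(1-p)/n).
- TEVAR, n = 50: √(0.42/50) = 0.092 at p = 0.3; √(0.50/50) = 0.100 at p = 0.5.
- EVAR, n = 60: √(0.42/60) = 0.084; √(0.50/60) = 0.091; at p = 0.1, √(0.18/60) = 0.055.

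By the exact hypergeometric distribution, a difference of at least 10 points has probability 28-32% in TEVAR and 32-36% in EVAR for p = 0.3-0.5.

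**Step 2: shift in the unadjusted difference.** Shift = imbalance × δ. For a one-SD imbalance in TEVAR this runs from 0.092 × 0.5 = 0.05 SD to 0.100 × 1.0 = 0.10 SD. The standard error is √(2V/n), with V from Step 3: √(2 × 1.0525/50) = 0.205 and √(2 × 1.25/50) = 0.224 SD.

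**Step 3: precision lost.** Without indication, the outcome variance is inflated by V = 1 + p(1-p)δ², which is also the sample-size ratio. The power column uses Φ(2.80/√V - 1.96), starting from a nominal 80%.

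| δ | V at p = 0.3 | V at p = 0.5 | Extra patients | 80% power becomes |
|---|---|---|---|---|
| 0.25 | 1.013 | 1.016 | 1-2% | about 79% |
| 0.5 | 1.0525 | 1.0625 | 5-6% | about 78% |
| 1.0 | 1.21 | 1.25 | 21-25% | 71-72% |

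At p = 0.1, V = 1 + 0.09δ², which gives about 0.6%, 2% and 9% extra patients.

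**Step 4: validity.** In a simulation of an unadjusted t test (40,000 runs per setting, p = 0.3 and 0.5, both cohort sizes), mean bias was about zero and two-sided type I error was 4.8-5.2%. Among runs with an imbalance of at least 10 points it was 5-9%. With at least 20 points it was 5-17%, the high end arising only at δ = 1.0.

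**The case against.** The best reply is that nothing is misstated. The covariate set is coherent, includes both stratification factors, and one more plausible covariate could be proposed for almost any trial. Chance imbalance is already reflected in the standard error, as Step 4 confirms. The cohorts are randomised and reported separately, which removes the abdominal-versus-thoracic split, and age may absorb part of any disease difference. All of this stands, and it limits the point to precision and to a shift conditional on the allocation that happens to occur.

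The prognostic premise is also thinner than it may seem. Data collection methods speaks of anatomical characteristics with a potential impact. No section says that disease type predicts recovery time. A reader might turn to the mortality figures in the Introduction (34% and 39%) as proof that the diseases differ. They do not serve: the first concerns ruptured aneurysm, which is excluded, and both include deaths before or during admission, largely outside the population enrolled.

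A reader might also infer that indication ought to be a subgroup, since the subgroups are introduced as a response to heterogeneity. The Discussion ties them to suspected risk factors for percutaneous failure, and aortic indication is not named there. A further subgroup in 100-120 patients would be weak and would not correct an imbalance.

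What survives is that the protocol treats disease characteristics as possibly prognostic, knows the indication for every patient, and does not use it where it could help.

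**Conclusion.** The point holds as a modest, nearly free gain in precision for recovery time and the continuous secondary outcomes. With 30-50% dissection, omitting indication costs 1-2% of the sample if the diseases differ by 0.25 SD, 5-6% at 0.5 SD and 21-25% at 1.0 SD. A typical imbalance in Cohort TEVAR shifts the difference by a quarter to just under half of a standard error when the disease effect is 0.5-1.0 SD (0.046/0.205 = 0.22; 0.100/0.224 = 0.45). The mix and the effect are both assumed. If dissection is rare, as it may be in Cohort EVAR, or the diseases recover alike, little is lost.

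A reader might infer that the primary recovery-time comparison is biased or invalid. The documents do not support that: allocation is randomised, and error rates hold over all randomisations. Nor does the point bear on the access-complication endpoint that sized the trial.

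**What to change.** In Analysis of primary and secondary outcomes, add indication (aneurysm or dissection) to the covariates of the adjusted GLM for the primary patient-centered outcome and the continuous secondary outcomes, in each cohort. Do this before any outcome data are seen, and so before the planned interim analysis; adding it after an imbalance has come to light would be post hoc. Protocol amendments already lists changes in statistical methods as a possible major amendment, so a route exists.

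The cost is one degree of freedom per model, roughly 1/100 = 1% of variance in a cohort of 100. At the 0.25 SD end of the range the change is therefore close to neutral, and above that it pays. No new data are needed, because the indication is established at eligibility. The unadjusted comparison, the randomisation and the subgroup list stay as they are; a third stratification factor in cohorts of this size would risk sparse strata.

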#### Sample size

As no previous studies reported PCOs, we used the incidence of access site complications to estimate the sample size of the SWEET trial. According to previous studies, the incidence of access site complications in percutaneous EVAR was 7.64%, compared with 11.81% in cutdown EVAR (13). We estimated the number of patients needed in this non-inferiority trial with non-inferiority margin of 0.10 (bilateral α 5%, power 80%) by PASS 15.0 software, and 54 patients are required for percutaneous and cutdown EVAR group, respectively. To allow for 10% drop out, 60 patients will be recruited per group, i.e., 120 for Cohort EVAR.

Previous TEVAR studies lacked solid data in above aspects, however, the relevant data of transcatheter aortic valve implantation (TAVI) can be used for reference due to their similar surgical approach (15). The incidence of access site complications was 8.7% in percutaneous TAVI and 8.5% in cutdown TAVI (16). The sample size was calculated with non-inferiority margin of 0.15 (bilateral α 5 %, power 80 %), 45 patients are required for percutaneous and cutdown TEVAR group separately. Fifty patients will be recruited each group allowing for 10% drop out, and the number of subjects in Cohort TEVAR is 100. Therefore, the total sample size of the SWEET trial is 220. The whole calculation process can be found in Supplementary Tables S3, S4 (Supplementary Material).

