### Statistical methods

#### Analysis population

As Cohort EVAR and Cohort TEVAR were powered and randomized separately, the statistical analysis of both cohorts is planned to be reported separately. The analysis populations of this trial involve modified intention-to-treat (ITT) and per-protocol (PP) populations. The modified ITT is determined after randomization and when the patient started endovascular aortic repair, hence all patients who indeed receive endovascular aortic repair are involved in the primary analysis within the respective access group as originally allocated. In this trial, the modified ITT will be the main analysis set for the summary of both ClinROs and PCOs data. Both ITT and PP analysis are required for test of non-inferiority, and PP analysis serves as a sensitivity analysis. The non-inferiority margin was predetermined at 10%, and the non-inferiority test will be evaluated as a two-sided test at alpha = 0.05. When non-inferiority is reached, ITT is further tested for superiority.

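### The sample sizes of 54 and 45 per group match one-sided 5%; at the stated two-sided 5% both cohorts have about 70% power, not 80%

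*Protocol article*

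**What the plan says.** All inputs are in the Sample size section of the protocol article.

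- **Cohort EVAR.** The planning rates are "the incidence of access site complications in percutaneous EVAR was 7.64%, compared with 11.81% in cutdown EVAR". The calculation uses a "non-inferiority margin of 0.10 (bilateral α 5%, power 80%) by PASS 15.0 software", and the result is that "54 patients are required for percutaneous and cutdown EVAR group, respectively". This becomes 60 per group after a 10% dropout allowance.
- **Cohort TEVAR.** The rates are borrowed from TAVI: "The incidence of access site complications was 8.7% in percutaneous TAVI and 8.5% in cutdown TAVI". The inputs and result are a "non-inferiority margin of 0.15 (bilateral α 5 %, power 80 %), 45 patients are required" per group, which becomes 50 after dropout.

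The Analysis population section repeats the significance level for the analysis itself: "the non-inferiority test will be evaluated as a two-sided test at alpha = 0.05". The article nowhere mentions a one-sided 5% level or a 90% confidence interval. It refers to Supplementary Tables S3 and S4 for the full calculation; these were not available.

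**The concern.** Non-inferiority is decided in one direction only: percutaneous access must not be worse than cutdown by the margin or more. A two-sided test at 0.05 is ordinarily read as comparing the upper limit of a 95% confidence interval with the margin, which puts 2.5% in the deciding tail. The article states this level both for the sample size and for the analysis, yet 54 and 45 look too small for it.

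Two things are at stake. If the trial is analysed as stated, its power for the primary clinician-reported endpoint is lower than claimed in both cohorts. If it is instead analysed as it appears to have been sized, the nominal risk of wrongly declaring non-inferiority is 5%, twice that of the stated test. A choice between the two that is left open until the data are seen could itself decide the conclusion.

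**Working it through.** **Inputs** (Sample size section). EVAR: pT = 0.0764, pC = 0.1181, margin m = 0.10. TEVAR: pT = 0.087, pC = 0.085, m = 0.15. Power is 80% and allocation 1:1. T is percutaneous, C is cutdown, and lower is better.

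**Formula** (unpooled variance, per group):

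n = (z_α + z_β)² × [pT(1 − pT) + pC(1 − pC)] / [m − (pT − pC)]²

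*Variance terms*
- EVAR: 0.0764 × 0.9236 + 0.1181 × 0.8819 = 0.0706 + 0.1042 = 0.1747
- TEVAR: 0.087 × 0.913 + 0.085 × 0.915 = 0.0794 + 0.0778 = 0.1572

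*Distance to the margin*
- EVAR: 0.10 + 0.0417 = 0.1417, squared 0.02008
- TEVAR: 0.15 − 0.002 = 0.148, squared 0.02190

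**Step 1: reproduce the article's figures.** With 5% in one tail, (1.645 + 0.842)² = 6.183.
- EVAR: 6.183 × 0.1747 / 0.02008 = 53.8, so 54
- TEVAR: 6.183 × 0.1572 / 0.02190 = 44.4, so 45

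Both match to the integer. The dropout step also agrees: 54/0.9 = 60 and 45/0.9 = 50.

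**Step 2: use the stated level.** With 2.5% in the deciding tail, (1.960 + 0.842)² = 7.849.
- EVAR: 7.849 × 0.1747 / 0.02008 = 68.3, so 69
- TEVAR: 7.849 × 0.1572 / 0.02190 = 56.3, so 57

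**Step 3: power at the stated level.** Power = Φ{[m − (pT − pC)] / SE − 1.960}, where SE = √(variance term / n).

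| Cohort | n per group | SE | Power |
|---|---|---|---|
| EVAR, after 10% dropout | 54 | 0.0569 | 70.2% |
| EVAR, no dropout | 60 | 0.0540 | 74.7% |
| TEVAR, after 10% dropout | 45 | 0.0591 | 70.7% |
| TEVAR, no dropout | 50 | 0.0561 | 75.2% |

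**Step 4: does another method rescue 54 and 45?** These are the numbers per group needed for 80% power with 2.5% in the deciding tail.

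| Method | EVAR | TEVAR |
|---|---|---|
| Pooled variance | 69 | 57 |
| Farrington-Manning | 78 | 69 |
| Continuity-corrected | 82 | 70 |
| Exact enumeration, unpooled Z-test | 66 | 58 |
| Exact enumeration, Farrington-Manning score | 76 | 67 |

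None gives 54 or 45. At those sizes, power is 73.3% (EVAR) and 73.6% (TEVAR) by exact enumeration of the unpooled Z-test, and 63.4% and 59.7% by the Farrington-Manning formula.

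**The case against.** No route was found from a bilateral 5% to 54 and 45, so the arithmetic itself is not in dispute. The objections concern how far the power figure can be taken.

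- **Unit of analysis.** The section on analysis of primary and secondary outcomes counts complications per femoral access, with GEE, whereas the calculation above is per patient. As an illustration, assume two accesses per patient, the planning rates applying per access, and within-patient correlation ρ. The effective size is then 2n/(1 + ρ). EVAR power with 54 patients per group would be 94% at ρ = 0, 82% at 0.5, 77% at 0.7 and 70% at 1, and it passes 80% when ρ is below about 0.58. This stands as a caveat: 70% is the power on the sponsor's own per-patient basis, not necessarily that of the GEE analysis. It does not rescue the stated 80%, because the article sizes in patients and gives neither the number of accesses per patient nor a correlation.
- **TEVAR margin.** The Analysis population section gives a single margin of 10%, while the TEVAR sample size uses 0.15. This is a separate conflict and only makes matters worse: at 0.10 the same formula gives about 38% power with 45 per group.
- **Unseen tables.** Supplementary Tables S3 and S4 may show which alpha was entered. They could explain the error, but they cannot make 54 and 45 correct for the level stated twice in the text.
- **A single figure hides a range.** This is fair. Across methods and dropout assumptions the per-patient figures run from about 60% to 76%. All are below 80%.

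**Conclusion.** The concern holds. The article's sample sizes correspond to one-sided 5%, and the article states two-sided 5% for both the design and the analysis. Two calculations with different rates and margins reproduce to the integer under the same one-sided setting, so rounding or coincidence is an unlikely explanation.

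At the stated level the requirement is 69 and 57 per group, a shortfall of 15 (EVAR) and 12 (TEVAR) evaluable patients per group. Power is about 70% and 71% with the planned evaluable numbers, and about 75% in each cohort if nobody is lost.

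These figures rest on the article's planning rates, a per-patient comparison, the unpooled formula that reproduces the article's own numbers, and a TEVAR margin of 0.15. The EVAR figure also depends on the assumed 4.17-point advantage for percutaneous access. The point must be fixed, because it affects the power claim for the primary clinician-reported endpoint in both cohorts.

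**What to change.** Keep the two-sided 0.05 test of the Analysis population section, and state there that non-inferiority is judged against the upper limit of a 95% confidence interval. In the Sample size section, replace the 80% claim with about 70% for EVAR (54 evaluable per group, margin 0.10) and about 71% for TEVAR (45 evaluable per group, margin 0.15), stated as per-patient figures. Check Supplementary Tables S3 and S4 for the alpha entered and bring them into line. Settle the TEVAR margin at the same time, since the restated TEVAR power depends on it.

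If one-sided 5% was really intended, both sections should say so, specify a 90% confidence interval, drop the bilateral and two-sided wording, and acknowledge the 5% risk of a false non-inferiority claim. Whichever is chosen should be fixed before the data are analysed.

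The cost is wording and, if the test is kept, a less favourable power figure. No new patients are needed. Restoring 80% at two-sided 5% would be a different decision. It would take 69/0.9 = 76.7, so 77 per EVAR group, and 57/0.9 = 63.3, so 64 per TEVAR group. That is 154 + 128 = 282 patients against the planned 220.

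### Cohort TEVAR is sized on an unexplained 15-point margin against an 8.5% control rate, while the analysis section states one 10% margin; if 0.15 decides, a non-inferiority verdict does not rule out a doubling of access complications

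*Protocol article*

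**What the plan says.** The Sample size section treats the two cohorts separately.

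- **EVAR:** complication rates of 7.64% (percutaneous) and 11.81% (cutdown). "We estimated the number of patients needed in this non-inferiority trial with non-inferiority margin of 0.10". The result is 54 per group, 60 after dropout.
- **TEVAR:** rates borrowed from transcatheter valve implantation because TEVAR data were lacking. "The incidence of access site complications was 8.7% in percutaneous TAVI and 8.5% in cutdown TAVI". "The sample size was calculated with non-inferiority margin of 0.15 (bilateral α 5 %, power 80 %), 45 patients are required" in each group, and "Fifty patients will be recruited each group allowing for 10% drop out".

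The text gives no clinical or statistical reason for 0.15, or for its being wider than the EVAR margin. It points to Supplementary Tables S3 and S4, but only for the calculation.

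The Analysis population section, under Statistical methods, gives one predetermined margin of 10%, tested two-sided at 0.05. It names no cohort, although it says that the cohorts are to be reported separately.

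**The concern.** The TEVAR margin is larger than the control rate that it is set against. The looser margin also belongs to the cohort with the lower assumed control rate, although the Outcome measures section gives both cohorts the same endpoints.

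The Introduction says that no randomised trial has compared the two accesses in TEVAR, so this cohort would give the first randomised verdict. The Discussion says that the comparison should serve clinical decision making. If the 15-point margin decides, a reader of a positive TEVAR result could not conclude from the verdict alone that a doubling of access complications had been ruled out. Which margin decides is itself unclear, because the sizing and analysis sections differ.

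**Working it through.** **Inputs.** From Sample size: TEVAR cutdown rate pC = 0.085, percutaneous rate pT = 0.087, margin m = 0.15, 45 evaluable and 50 recruited per group; EVAR pC = 0.1181, m = 0.10. From Analysis population: margin 10%, two-sided 0.05. The 1.5-fold and 2-fold rises are chosen here for illustration and are not in the protocol.

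**1. The stated size.** n = (z_α + z_β)² × [pT(1−pT) + pC(1−pC)] / [m − (pT−pC)]².

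- Variance sum: 0.087×0.913 + 0.085×0.915 = 0.0794 + 0.0778 = 0.1572.
- Distance: 0.15 − 0.002 = 0.148; squared, 0.0219.
- One-sided 5%: (1.645 + 0.842)² × 0.1572 / 0.0219 = 44.4, so 45, and 45/0.9 = 50. This matches the plan.
- One-sided 2.5%, the usual reading of a two-sided 5%: (1.960 + 0.842)² × 0.1572 / 0.0219 = 56.3, so 57. This does not match.

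The plan's 45 therefore comes from the 0.15 margin at one-sided 5%. The results in steps 3 and 4 use the stated two-sided 5% unless noted.

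**2. Where the margins lie.**

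| Cohort and margin | Limit | Ratio to control |
|---|---|---|
| TEVAR, 15 points | 8.5% + 15 = 23.5% | 2.76 |
| TEVAR, 10 points | 8.5% + 10 = 18.5% | 2.18 |
| EVAR, 10 points | 11.81% + 10 = 21.81% | 1.85 |

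The TEVAR margin is 0.15/0.085 = 1.76 times the control rate. A doubling, 8.5% to 17%, is 8.5 points and lies inside 15.

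**3. Chance of declaring non-inferiority.** All pairs of binomial counts are enumerated, with one observation per patient. The rule passes when the observed difference plus 1.96 × √[pT(1−pT)/n + pC(1−pC)/n], with observed rates inside the root, is below m. The control rate is 8.5%.

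| True percutaneous rate | m = 0.15, n = 45 / 50 | m = 0.10, n = 45 / 50 |
|---|---|---|
| 8.7% (design) | 73.6% / 76.3% | 39.7% / 43.9% |
| 12.75% (1.5-fold) | 42.9% / 44.2% | 15.7% / 17.2% |
| 17% (2-fold) | 18.8% / 18.5% | 4.8% / 5.0% |

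For comparison, a 1.5-fold rise in EVAR (10 points, 54 / 60 per group) passes 9.9% / 10.4% of the time.

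**4. Sensitivity, m = 0.15.**

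- Normal approximation: for the 1.5-fold rise at n = 45, SE = √[(0.0778 + 0.1112)/45] = 0.0648, and Φ[(0.15 − 0.0425)/0.0648 − 1.96] = 38%. At n = 50 it is 42%.
- Newcombe limit: 35-36% for the 1.5-fold rise and about 15% for a doubling.
- Farrington-Manning test: 32-36% and 14-15%.
- Wald at one-sided 5%, the level that reproduces n = 45: 52-56% and 26-28%.

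**5. Size at 10 points.** With m = 0.10 the distance is 0.098. Then 80% power at 8.7% versus 8.5% needs 129 per group at two-sided 5%, or 102 at one-sided 5%.

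**The case against.** The strongest reply is that 0.15 appears only as a sizing input. The only stated decision rule is the 10% in Analysis population, and under it the 1.5-fold case passes 16-17% of the time. This stands: the larger probabilities hold only if the conflict is settled in favour of 0.15. A reader might infer that the plan as written would pass a 1.5-fold harm about four times in ten. The documents do not support that without this condition.

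A reader might also take these probabilities for false-positive rates. They are not. Rises of 4.25 and 8.5 points lie inside either margin, so passing them is correct by the margin's definition. At a true 23.5%, the rule passes only 3.0-3.5% of the time. The figures show what the margin tolerates, not a failure of error control.

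A third reply is that 10 points is no cure: it too exceeds 8.5% and does not exclude a doubling. This also stands. The case for 10 points is that the protocol already states it, and that it falls less far from the control rate.

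The choice of margin is partly a clinical judgement. The composite includes minor events such as blood on a dressing, and 8.5% is a proxy from another procedure. Complications are to be analysed per femoral access, so the effective sample size may differ from the per-patient figures. These points limit the precision of the probabilities. They do not explain why TEVAR has the wider margin. A reason may stand in the supplement, which is not shown, so the finding is that none appears in the text, not that none exists.

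**Conclusion.** The concern holds in conditional form. On the protocol's own figures, Cohort TEVAR is sized to a limit of 23.5%, 2.76 times the assumed control rate. No reason is shown, the margin is looser than EVAR's, and the analysis section gives 10%. If 0.15 is the decision margin, a doubling passes about 19% of the time and a 1.5-fold rise about 43-44%. If 10% is, these fall to about 5% and 16-17%, but power at the design rates is then about 40-44%, not 80%.

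These figures assume an 8.5% control rate, a two-sided 95% Wald limit, 45-50 per group and one observation per patient. The limits in step 2 depend only on the assumed control rates and the margins. Either way of settling the conflict requires a change to the text.

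**What to change.** Reconcile Sample size with Analysis population, naming the margin for each cohort. There are two routes.

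1. **Apply the stated 10% to TEVAR.** Keep 50 per group, replace the 80% by about 40-44% power at 8.7% versus 8.5% (two-sided 5%), and present TEVAR mainly as a risk difference with its 95% confidence interval.
2. **Keep 0.15.** Give its clinical reason, and state it as the TEVAR margin in Analysis population. Limit the permitted conclusion to saying that an increase of more than 15 percentage points is excluded, with the interval reported and without an unqualified claim of non-inferiority.

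Report the interval in either case, because a 10-point margin is itself wide (limit 18.5%, about 2.2-fold).

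The cost is a wording amendment, with no extra patients or procedures. The real price is a much lower stated power under the first route, which makes TEVAR largely an estimation study, or a weaker permitted claim under the second. Restoring 80% power at 10 points would take 129 evaluable patients per group at two-sided 5%; that is not proposed here.
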